## Abstract

**Background:**

Cancer diseases and their therapies have negative effects on the quality of life. The aim of this study is to assess the effectiveness of case management in a sample of oncological outpatients with the intent of rehabilitation after cancer treatment. Case management wants to support the complex information needs of the patients in addition to the segmented structure of the health care system. Emphasis is put on support for self-management in order to enhance health - conscious behaviour, learning to deal with the burden of the illness and providing the opportunity for regular contacts with care providers. We present a study protocol to investigate the efficacy of a case management in patients following oncology rehabilitation after cancer treatment.

**Methods:**

The trial is a multicentre, two-arm randomised controlled study. Patients are randomised parallel in either 'usual care' plus case management or 'usual care' alone. Patients with all types of cancer can be included in the study, if they have completed the therapy with chemo- and/or radiotherapy/surgery with curative intention and are expected to have a survival time >1 year. To determine the health-related quality of life the general questionnaire FACT G is used. The direct correlation between self-management and perceived self-efficacy is measured with the Jerusalem & Schwarzer questionnaire. Patients satisfaction with the care received is measured using the Patient Assessment of Chronic Illness Care 5 As (PACIC-5A). Data are collected at the beginning of the trial and after 3, 6 and 12 months. The power analysis revealed a sample size of 102 patients. The recruitment of the centres began in 2009. The inclusion of patients began in May 2010.

**Discussion:**

Case management has proved to be effective regarding quality of life of patients with chronic diseases. When it comes to oncology, case management is mainly used in cancer treatment, but it is not yet common in the rehabilitation of cancer patients. Case management in oncology rehabilitation is not well-established in Switzerland. A major challenge of the study will therefore probably be the recruitment of the patients due to the physicians' and patients' scarcely existing awareness of this issue.

**Trial registration:**

ISRCTN41474586

## Background

Cancer diseases and their therapies have short- and long-term negative effects on the quality of life. Thus, it is important to offer patients targeted rehabilitation and integrated care [1]. Analyses of 'survivors' after a five-year survival time revealed various psychosocial problems with impact on the patient's quality of life and career depending on the illness and care received [2,3]. Since cancer diseases develop into chronic conditions, patients not only expect physical rehabilitation, but also a broad range of services offered to develop skills which can enable them to cope with the long term consequences of cancer diseases [4,5]. For this reason provision of individual- and group-oriented rehabilitation programs satisfies the patients' demands for continuity in care and for encouragement to develop self-management skills as described in the Chronic Care Model of the World Health Organization (WHO) [6,7]. This is in accordance with Bergeson et al [8], who call for an efficient care network for the chronically ill to contain the following: 1. Access to and continuity in care, 2. Close involvement of patients in the provision of their own care, 3. Supportive measures for self-help or self-management, respectively, 4. Coordination of care between individual institutions and service providers.

Ambulant rehabilitation following cancer therapy is not well established in Switzerland. Despite the fact that psychosocial counselling, psycho-oncological therapy and opportunities to increase physical fitness are widely offered, the needs of the patient cannot be met. According to patient surveys the following problem areas were defined: inadequate information on side-effects and on consequences of the acute treatment, lack of process in communication, problematic transition from acute care to aftercare and rehabilitation, serious economical consequences and insufficient preparation for return to work. Patients value additional information and support on the following topics: information on cancer diseases, conduct in case of therapy and handling thereof in daily life, an overview of offers of support and counselling, advice on and guidance in matters related to pain, fatigue, dietary change, hair loss, and complementary or alternative medical therapies [9-12]. Similarly, patients expect to be offered physical movement programs and counselling on psychological strain and the resumption of daily chores/work, financial matters and worries, as well as counselling for relatives. Patients in rehabilitation have the following objectives: physical fitness, dietary changes, weight reduction and capacity to deal with psychological stress. They have the following expectations of their doctors: holistic understanding of rehabilitation with coordinated services offered targeting the various aspects of quality of life, information on rehabilitation services offered, reintegration into everyday and professional life [9-12]. Dissatisfaction of the patient does not arise due to a lack of rehabilitation and advisory services, but rather due to insufficient information on existing offers and failure of doctors to document their needs and consecutively failure to refer them to the appropriate therapeutic and counselling services. After cancer therapy, many patients do not have the energy to get themselves the necessary information they need and to claim for support. Case management, where a case manager (rehabilitation coach) provides coordination and exchange of relevant information between doctors and other care providers, is therefore one way to tackle these problems actively.

## Case Management

Case management (CM) used in the care of the chronically ill, is described in several ways; targets and interventions range from coordinating multidisciplinary therapies with adequate provision of the relevant information to patients and therapist to the assessment of patients' needs and thus the appropriate interventions. Case management can function as a communication centre for all parties involved, but can also serve as a main contact person (primary nurse) [13-16]. Consequently, CM wants to support the complex information needs of the mostly chronically ill patients taking into account the segmented structure of the health care system [13]. Hence, emphasis is put on support for and activation of self-management in order to enhance health- conscious behaviour, learning to deal with the burden of the illness and providing the opportunity for regular contacts with care providers. This approach is part of the Chronic Care model of the WHO. CM is a collaborative process adhering to a system, that tries to compile patient needs and resources, goals of rehabilitation, planning and execution of interventions and evaluations in collaboration with the patient, and, if necessary with their relatives. Considering oncology, CM is successfully applied in the follow-up after therapies and can help to improve the recording of cancer treatments and its symptoms [17,18]. However, a systematic review comprising seven trials found no concluding evidence regarding the effectiveness of case management due to differences in interventions and trial endpoints [19].

### Fostering self-management

It is assumed that the fostering of self-management helps patients to manage the rehabilitation phase more easily and to develop skills to improve their health status. Adequate self-management requires a lot from the chronically ill patient. Suffering from cancer often causes mental stress, fear, uncertainty and insecurity for one's life and future. Effective self-management programs aim to support patients in developing strategies to positively improve their health status. The encouragement of self-efficacy is a relevant concept, that means to promote an optimistic outlook as well as faith in the ability to handle new or difficult situations by means of one's own competence [20]. Many patients need additional counselling and coaching to develop the skills needed to deal with the sequels of illness and medication, with stress and other emotional strain; dietary changes; the promotion of physical fitness through exercise; the continuation or adjustment of the patient's role in the family, and in their professional and daily life. The following five elements in self-management programs should be encouraged the most: problem solving; decision making; use of resources; building a relationship between patient and care team; implementation of an action plan [21].

## Methods

### Objectives

The primary goal of the trial is to assess whether the quality of life of cancer patients with usual care plus case management is significantly better compared to usual care alone one year after a first therapy.

#### Secondary outcomes

a) ability to work recorded in days of sick leave

b) self-efficacy

c) planned health care utilisation (general practitioner/oncologist, specialists and hospitalisation), illustrated as number of contacts

d) unplanned consultations (general practitioner/oncologist, specialists and hospitalisation), illustrated as number of contacts that were unplanned

e) Satisfaction with medical care

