### Inclusion criteria for patients

a) Age ≥18 years

b) Completion of a therapy with chemo- and/or radiotherapy/surgery (longer term hormone and antibody therapy are excluded)

c) Therapy with curative intention

d) Patients with an expected survival time >1 year

e) Increased distress score (3-7 on the Distress Thermometer Likert scale)

f) Intention to undertake ambulant rehabilitation

g) Rehabilitation need/prevailing strain

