### Measurements

#### Patient characteristics

Demographics include age, gender, education, race/ethnicity, family status, employment status

Medical characteristics include diagnosis and therapies, time since cancer diagnosis, other diagnosis and therapies, supportive therapies.

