### Outcome measures

To determine the health-related quality of life (primary outcome), the general questionnaire FACT G version 4 is used. It contains a summary of 27 items divided into four primary focal points relating to quality of life.

To measure secondary outcomes such as ability to work, the days of sick leave will be recorded at work, as well as the help needed with daily chores. The direct correlation between self-management and perceived self-efficacy is measured with the Jerusalem & Schwarzer questionnaire [23]. The satisfaction of patients with the care received is measured using the Patient Assessment of Chronic Illness Care (PACIC 5-A), which has been developed to assess congruency of provided health care to the Chronic Care Model (CCM). Table 2 gives an overview of the measuring tools for the primary and secondary outcomes (table 2). Data is collected at the beginning of the trial, and after 3, 6 and 12 months.

**Table 2 T2:** Overview of measuring tools/measuring time

Outcomes	Measuring tool	Point in time
**Primary Outcome** Quality of life	FACT G	Months 0, 3, 6, 12

**Secondary Outcomes**		Months
Employability	Questionnaire	0, 3, 6, 12
Self - efficacy Unplanned consultations (GP/oncologist, specialist) and hospitalisation Satisfaction with medical care Type, number of rehabilitation measures	Questionnaire self-efficacy expectation by Jerusalem & Schwarzer Number of consultations/rehabilitation- and support measures Questionnaire PACIC 5-A Questionnaire- patient logbook	

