### Statistical analyses

Continuous primary and secondary outcomes will be checked by the Shapiro-Wilk test for normality distribution and data are expressed by means with standard deviations and medians with interquartile range as appropriate. Categorical variables will be expressed as percentages. Primary and secondary outcomes will be compared between groups to investigate the effect of the case management on oncology rehabilitation using parametric or non-parametric tests as appropriate. Categorical outcomes will be analysed by Chi Square tests. To control for any imbalance between groups multiple regression analysis will be used and measures that show any difference in baseline characteristics will be included into the model as potential confounders.

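### Days of sick leave stop accruing when a patient leaves work, so the ability-to-work outcome can count against the arm that keeps more patients in their jobs

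*Protocol article*

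**What the plan says.** All references are to the protocol article.

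- **Definition.** Secondary outcomes, first item: "a) ability to work recorded in days of sick leave".
- **Recording.** Outcome measures: "the days of sick leave will be recorded at work, as well as the help needed with daily chores". Table 2 lists the outcome as "Employability", collected by questionnaire at months 0, 3, 6 and 12, without describing the items.
- **Eligibility.** "a) Age ≥18 years", with no upper age limit. Neither the inclusion nor the exclusion criteria mention employment.
- **Employment status.** It is collected: "Demographics include age, gender, education, race/ethnicity, family status, employment status". It is not linked to the work outcome.
- **Analysis.** "Primary and secondary outcomes will be compared between groups to investigate the effect of the case management on oncology rehabilitation". No population is named for the work outcome. Adjustment is planned only at baseline: "measures that show any difference in baseline characteristics will be included into the model as potential confounders".

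The Background names effects on career and poor preparation for return to work among the problems of these patients. The section on fostering self-management lists the patient's professional role among the matters for which many patients need coaching.

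**The concern.** The construct is ability to work, and the stated measure is a count that can grow only while a person has a job. Two groups fall outside it.

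1. **Patients without a job at baseline**, such as retired patients. They have no sick leave to record. If they entered as zero days, they would hold the best possible value for a reason unrelated to treatment.
2. **Patients who leave work for health reasons during follow-up.** Their sick leave stops at exit, although their work outcome is among the worst.

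The second group matters more. Helping patients stay in work is a plausible effect of case management. If it does so, the intervention arm has more people still able to accrue sick leave, and the comparison is biased against it. If more patients left work under case management, the bias would run in its favour.

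**Working it through.** **The plan's own figure.** The only calculated figure is the sample size for FACT: difference 3.0, SD 5.4, alpha 0.05, power 0.80. The normal-approximation formula, two-sided, gives 51 per arm and 102 in total (power 0.801), so the stated 102 reproduces. It does not bear on sick leave, but 51 per arm is used below.

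**Inputs for the illustration.** The documents give no employment rate, mean sick leave or job-exit rate. All such values here are assumed.

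**Step 1: patients not employed at baseline, counted as zero.** Let *e* be the employed share and let mean days among those in work be 90 (control) and 70 (case management).

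Difference = *e* × (70 − 90).

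At *e* = 0.4, 0.6, 0.8 and 1.0 this is −8, −12, −16 and −20 days. The effect shrinks in proportion to *e* and keeps its sign.

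A chance imbalance in employed share adds noise. At *e* = 0.6 and 51 per arm, the SD of the between-arm difference in share is √(2 × 0.6 × 0.4 / 51) = 0.097. That is 0.097 × 90 = 8.7 days.

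A second assumed set shows the loss of power: means 120 and 75 among the employed, SD 90, 51 per arm, two-sided t-test at 0.05.

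| Not employed | Difference, all patients | Power, all patients | Power, employed only |
|---|---|---|---|
| 20% | 0.8 × 45 = 36 days | 52% | 61% |
| 40% | 0.6 × 45 = 27 days | 35% | 49% |
| 50% | 0.5 × 45 = 22.5 days | 28% | 42% |

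Under these inputs the smaller employed group has more power than the full sample with zeros.

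**Step 2: exit from work after randomisation.** Let *x* be the share of employed patients who leave work. As a simplification, leavers contribute zero days.

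Arm mean = *e* × (1 − *x*) × mean days among those in work. With *e* = 0.6:

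| Days in work (control / CM) | Exit (control / CM) | Control mean | CM mean | Difference |
|---|---|---|---|---|
| 90 / 70 | 20% / 20% | 43.2 | 33.6 | −9.6 |
| 90 / 70 | 20% / 5% | 43.2 | 39.9 | −3.3 |
| 90 / 70 | 30% / 5% | 37.8 | 39.9 | +2.1 |
| 90 / 90 | 20% / 5% | 43.2 | 51.3 | +8.1 |

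The sign changes when the share staying in work is more than 90/70 = 1.29 times higher with case management. At 20% versus 5% exit the ratio is 0.95/0.80 = 1.19, so no reversal. At 30% versus 5% it is 0.95/0.70 = 1.36, so the sign reverses. The employed share *e* multiplies both arms and does not affect the sign. Restricting to employed patients (*e* = 1) still gives 63.0 versus 66.5 at 30% versus 5% exit. The restriction alone does not cure the problem.

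**Step 3: a bound on the shift.** A patient leaving at month 3 misses at most 365 × 0.75 ≈ 274 days. If exit differs by 10 points across all patients, the shift is at most 0.10 × 274 ≈ 27 days. That is a ceiling, because it assumes the leaver would have been on sick leave every remaining day. At a rate of 120 days a year the loss is 120 × 0.75 = 90 days, and the shift is 9 days. With 60% employed and the 10 points applied to them only, the ceiling is 0.6 × 27.4 ≈ 16 days.

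**Step 4: other ways to handle leavers.** Setting them to missing compares only those who stayed in work, a group selected after randomisation and possibly by the intervention. Baseline adjustment cannot repair this, nor the zero count, because the exit happens after baseline.

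**Step 5: counting days not worked.** Take employed patients, 30% versus 5% exit at month 3, and the 274 remaining days as not worked. Days before exit are left out for leavers, as in Step 2. Control is 0.70 × 90 + 0.30 × 274 = 145.2. Case management is 0.95 × 70 + 0.05 × 274 = 80.2. The direction now agrees with the work outcome.

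**The case against.** The strongest reply is that the article never says patients without a job score zero, nor that every randomised adult enters this comparison. Not applicable is at least as natural a code for a pensioner. Denominators and coding of a secondary outcome commonly sit in the full protocol or analysis plan, which are not shown. This stands. A reader might infer that retired and non-employed patients receive the best score and push the result the wrong way. The documents do not support that: their coding is unstated, and Step 1 shows that zeros at baseline would dilute the effect without reversing it.

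It is also fair that sick leave is not the only work-related item. Help with daily chores and an employability questionnaire are collected, and employment status would enter the regression if it differed at baseline. These points limit the problem but do not remove it, because the secondary outcome itself is still defined as sick-leave days.

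Finally, reversal needs a sizeable difference in exit, and the documents give no exit rate. That also stands, so reversal is a possibility and not a prediction. However, the bias starts with any difference in exit. An analysis plan could restrict the population, but it could not make sick-leave days register job loss without changing the stated measure.

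**Conclusion.** The point holds for exit from work after randomisation. The stated measure can reward leaving a job through ill health. If case management keeps more patients in work, the comparison is biased against it, and the sign can change when exit differs enough between arms. Under the assumed 90 and 70 days, that means a retention ratio above 1.29. Baseline adjustment does not help, and setting leavers to missing replaces one bias with another. For patients not employed at baseline, the most that can be said is that counting them as zero, if that were done, would dilute the effect and add chance imbalance.

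Every magnitude rests on assumed figures, and the 27-day shift is an upper bound. One secondary outcome is affected; the primary comparison on FACT is not. This is a cheap improvement.

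**What to change.** Redefine the first secondary outcome as follows.

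1. **Population:** patients in employment at baseline, including those on sick leave from a job, identified from the employment status already collected.
2. **Measure:** days not worked for health reasons up to month 12. Job loss, disability pension or early retirement on health grounds then counts as not working.
3. **Companion result:** the proportion working at 12 months, by arm.
4. **Patients not employed at baseline:** report the help-with-daily-chores item separately.

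The first two changes are needed together, since Step 2 shows that the restriction alone leaves the bias in place. The cost is the wording of one outcome, one clarifying item on the reason for leaving work in the existing questionnaire, and a smaller denominator for this outcome.

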### Design

The trial is a multicentre, two-arm randomised controlled study. Patients are randomised parallel in either 'usual care' plus case management or 'usual care' alone.

### Participants

It was originally intended to include patients with breast and colon cancer after completion of an adjuvant therapy. Due to difficulties in the recruitment of enough patients, the inclusion criteria, following agreement with the Ethics Committee, were extended. Patients with all types of cancer fulfilling the inclusion criteria can be included. Eleven oncological centres in the Canton of Zurich participate in the recruitment of patients.

### Inclusion criteria for patients

a) Age ≥18 years

b) Completion of a therapy with chemo- and/or radiotherapy/surgery (longer term hormone and antibody therapy are excluded)

c) Therapy with curative intention

d) Patients with an expected survival time >1 year

e) Increased distress score (3-7 on the Distress Thermometer Likert scale)

f) Intention to undertake ambulant rehabilitation

g) Rehabilitation need/prevailing strain

### Exclusion criteria for patients

a) Patients with metastasis and/or cancer in an advanced stage with palliative therapy

b) Patients with an expected survival time ≤1 year

c) Patients with insufficient knowledge of the German language to participate in counseling and evaluations

d) Patients with severe psychiatric diagnoses or apparent great distress requiring medical psychiatric treatment

e) Completion of therapy longer than one month ago

### Exclusion from study

In case of a relapse or progression of the condition with deterioration of the quality of life and therapy, the patient will leave the study. For ethical reasons, case management will be continued if requested by the patient.

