### Patient informed consent

Prior to study participation patients receive written and oral information about the content and extent of the planned study; for instance about potential benefits for their health and potential risks. In case of acceptance they sign the informed consent form.

In case of study discontinuation all material will be destroyed or the patient will be asked if he/she accepts that the existing material can be used for the study.

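### Follow-up for the primary quality-of-life outcome stops at relapse with deterioration, an event defined partly by that outcome

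*Protocol article*

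**What the plan says.** The objective, set for the one-year point following initial treatment, is to test whether "quality of life of cancer patients with usual care plus case management is significantly better compared to usual care alone" (Objectives). The instrument is fixed under Outcome measures: "To determine the health-related quality of life (primary outcome), the general questionnaire FACT G version 4 is used". The schedule is in the same section: "Data is collected at the beginning of the trial, and after 3, 6 and 12 months".

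Exclusion from study stands apart from the eligibility criteria and applies to patients already in the trial. In case of "relapse or progression of the condition with deterioration of the quality of life and therapy, the patient will leave the study". It then adds: "For ethical reasons, case management will be continued if requested by the patient". What ends is study participation, not necessarily the intervention.

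Patient informed consent adds: "In case of study discontinuation all material will be destroyed or the patient will be asked" whether what exists may be used. Study discontinuation is not defined there, and the sentence is not linked to the relapse rule.

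Statistical analyses plans between-group tests, with regression to adjust for baseline differences. Sample size expects 30% drop-out and attributes it to how ill the patients are.

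**The concern.** Worsening quality of life is part of the trigger for leaving, and quality of life is what the trial compares. Patients who meet the trigger give no further FACT-G scores, so the 12-month comparison is confined to patients selected after randomisation, partly on the outcome.

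Removal could differ between arms by two routes. Table 1 gives the case-management arm telephone contact at least monthly for the first six months, on top of usual care, whose follow-up is usually quarterly; deterioration might be noticed at different rates. And if case management helps, fewer of its patients would meet the quality-of-life part of the trigger. Adjustment for baseline differences does not undo selection that happens after randomisation.

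This is a rule about data collection, not a detail left to an analysis plan. An intention-to-treat statement elsewhere could not restore scores that were never collected or were destroyed.

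**Working it through.** **Inputs from the protocol article (Sample size).** Target difference 3.0, SD 5.4, significance level 0.05, power 0.8. Two-sided testing and 1:1 allocation are assumed; the article states neither.

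**The plan's own figure.** n per arm = 2 × (1.960 + 0.842)² × 5.4² / 3.0² = 2 × 7.85 × 3.24 = 50.9, so 51 per arm and 102 in total. This matches the stated 102, so 3.0 and 5.4 are a sound yardstick for what follows.

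**Inputs that must be assumed.** The article gives no relapse rate, no removal rate by arm and no fall in score at relapse. I take removal of 5% to 20% per arm, and a gap between retained and removed patients of 5.4 to 8.1 points (1 to 1.5 SD).

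**Bias formula.** Let m be the share removed in an arm and g the mean of retained minus the mean of removed patients. The full-arm mean is (1 − m) × retained + m × removed, so the retained mean exceeds the full-arm mean by m × g. The error in the between-arm difference (T case management, C usual care) is

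bias = m_T × g_T − m_C × g_C.

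With the same gap in both arms:

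| Removed, case management | Removed, usual care | Bias, gap 5.4 | Bias, gap 8.1 |
|---|---|---|---|
| 10% | 10% | 0 | 0 |
| 5% | 10% | −0.05 × 5.4 = −0.27 | −0.05 × 8.1 = −0.41 |
| 10% | 5% | +0.27 | +0.41 |
| 10% | 20% | −0.10 × 5.4 = −0.54 | −0.10 × 8.1 = −0.81 |
| 20% | 10% | +0.54 | +0.81 |

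A positive sign favours case management. Against the target of 3.0, the non-zero entries run from 0.27/3.0 = 9% to 0.81/3.0 = 27%.

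**Simulation of a joint trigger.** Control mean 22.7, true difference 3.0, SD 5.4, equal relapse risk in both arms, a 5.4-point fall at relapse, and removal only if the patient has relapsed and scores below 22.7. The threshold is my assumption; the article gives none.

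| Relapse risk | Removed, usual care | Removed, case management | Difference among retained |
|---|---|---|---|
| 5% | 4.2% | 3.3% | 2.99 |
| 10% | 8.4% | 6.7% | 2.97 |
| 20% | 16.8% | 13.4% | 2.92 |
| 30% | 25.2% | 20.2% | 2.89 |

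With no true effect, the difference among retained patients stays at 0. Under equal relapse risk and equal detection, the loss is therefore small (at most 0.11 points, about 4%). Larger shifts need removal rates that differ between arms without an offsetting difference in the score gap.

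**The case against.** The strongest objection is that the trigger is joint. A patient leaves only on relapse or progression together with deterioration and therapy; a low FACT-G score alone removes nobody, and no FACT-G cut-off is given. This stands. A reader might infer that the rule cuts off the low end of the score distribution and so markedly shrinks a true effect. The text does not support that: it is not a rule on low scores, and the simulation of a joint trigger moves 3.0 only to about 2.9.

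A reader might also infer that closer contact means more relapses are detected under case management, so that the bias favours it. The documents do not establish this. Both arms have oncologist and GP follow-up of the illness, usually quarterly; the coach counsels and coordinates and is nowhere said to diagnose relapse; monthly calls are set only for the first six months and may then be reduced. Since therapy is part of the trigger, the relapse has presumably been recognised already, in either arm. Entry is restricted to curative intent without metastasis, which argues against assuming a high relapse rate.

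Nor does the consent section say that relapsed patients' data will be destroyed. Its wording is either/or, and applying it to patients removed for relapse is a plausible reading, not a stated one.

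Finally, month-3 and month-6 scores collected before removal remain usable where the patient agrees, and the analysis population and missing-data handling may be set out in a document not shown. That is fair, and their absence here is no criticism. It does not reach scores that the rule itself prevents from being collected.

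**Conclusion.** The concern holds in a limited form. The protocol ends follow-up for its primary outcome on a post-randomisation event defined partly by that outcome, and it allows discontinuers' existing data to be destroyed, without saying whether that includes patients removed after relapse. The one-year comparison is then not between the groups as randomised, and what is uncollected or destroyed stays lost.

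Neither size nor direction can be determined from the documents. On the assumed inputs the bias is nil with equal removal and equal score gap, and about 0.3 to 0.8 points either way for removal of 5% against 10% or 10% against 20%, compared with a target of 3.0. These are illustrations, not estimates. I would class the change as a cheap improvement: worth making before patients leave, but not proof that the trial's result would be materially wrong.

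**What to change.** In Exclusion from study, replace the instruction that the patient leaves with wording such as: *the relapse or progression and its date are recorded; the patient stays in follow-up, continues to receive the 3-, 6- and 12-month questionnaires unless consent is withdrawn, and is analysed in the randomised arm.* Report an analysis restricted to relapse-free patients as a sensitivity analysis only. Clinical care, including the provision on continuing case management, is untouched.

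In Patient informed consent, state that data collected up to discontinuation are kept unless the patient, when asked, refuses, and that arm, date and reason are retained as far as consent allows. Say also whether this section applies to patients who relapse.

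The cost is a short amendment, revised consent wording and a few more questionnaires. Patients already mail these directly to the study centre, so no extra visits are needed. The downsides are some burden on relapsed patients and a slightly more variable outcome.
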